### Data collection and management

After obtaining informed consent, an independent research assistant will initiate baseline information collection one day before surgery. All personal information will be kept strictly confidential for research purposes only. Basic demographic information, including gender, age, vital signs, body mass index, past medical history, family history, smoking and drinking history, allergy history, operation history or anesthesia history, medication history, age-adjusted Charlson comorbidity index (aCCI, a widely used scoring system to predict outcomes of variety of medical conditions and malignancies, including the age of the patient as a correction variable of the final score of the CCI with the addition of one point for every decade over 40 years), ASA classification, KPS, Glasgow coma scale (GCS) will be collected. Functional classification of tumor (indicating the resectability of tumor) will be evaluated according to the results of preoperative MRI (Supplementary Table 4) [31, 32].

Intraoperative viable include vital sign parameters during anesthesia, total dose or infusion rate of anesthetic agents or other drugs during operation, such as inotropic or vasoactive drugs, mannitol, estimated blood loss, urine volume, the type, and dose of fluid and blood transfusion, duration of surgery and anesthesia. The usage of the analgesia pump (dosage, number of compressions, and effective compressions) will be recorded.

Postoperative medication will be recorded including sedative, analgesia, glucocorticoids, mannitol, and fluid infusion on 1 to 3 days postoperatively. The extent of resection (EOR) will be evaluated by a professional neuro-radiologist according to the results of the MRI within 72 h postoperatively (Supplementary Table 4).

The median follow-up time will be 18 months postoperatively before the study was terminated. The patients and their legal representatives will be told to be followed up by telephone at 3, 6, 9, 12, 15, and 18 months postoperatively. The start points of simultaneous radiotherapy and chemotherapy, patient compliance, adverse events or complications and treatment, the European organization for the research and treatment of cancer on quality of life (EORTCQLQ-C30), and the Karnofsky performance Status (KPS) Scale will be evaluated every 3 months postoperatively. Strict data management will be kept including double data entry and establishing range checks for data values.

### Sample size calculation and statistical analysis

The sample size is estimated by using PASS 2011 software (NCCS LLC). We calculated the sample size based on the primary outcome. A two-sided Log-rank test with an overall sample size of 344 subjects (172 in the intravenous group and 172 in the inhalation group) achieves 80% power at a 0.05 significance level to detect a hazard ratio of 1.66 when the overall survival is 15 vs. 11 months in intravenous and inhalation group, respectively. The study will last for about 42 months, of which subject accrual (entry) occurs in the first 24 months with the proportion dropping out of the two groups being 0.1, respectively.

Analysis will be conducted using SPSS software (version 23.0). The Kolmogorov-Smirnov test will be used to test data normality. Normally distributed continuous variables will be described as the means with standard deviation (SD) and compared by using independent *t* tests. Non-normally distributed variables will be summarized as medians and interquartile range (IQR) and compared by using Mann-Whitney *U* tests. Categorical variables will be described as numbers (*n*) and percentage (%) and compared using chi-square or Fisher’s exact tests.

The Kaplan-Meier method will be used to describe the time-to-event data (OS and PFS), and the log-rank test will be used for comparisons. Univariate and multivariate Cox proportional hazard regressions will be used for survival analysis. Together with the anesthesia type, variables with *P*<0.1 in the univariate analysis will be regarded as candidate variables for the multivariable model. A significance level of *P*<0.05 will be used to indicate statistical significance. The imputation method will be used for dealing with missing data. The impact of missing data will be estimated by sensitivity analysis. Additionally, subgroup analysis will be undertaken to assess the association between anesthesia and the outcome according to the aCCI, KPS, EOR, WHO grade, duration of anesthesia, and whether using chemotherapy or not. No interim analysis will be done and the trial will not early terminate.

The patients receiving reoperation for postoperative complications with different anesthesia methods will be analyzed with the intention-to-treat principle, a secondary per-protocol analysis where patients with protocol deviations are removed. The patients whose postoperative pathological results excluded high-grade glioma will be analyzed with the per-protocol principle. The patients of dropouts, lost follow-up, or end of the study will be treated as censoring in survival analysis.

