## Discussion

This is a randomized controlled trial to compare the effect of intravenous or inhalation anesthesia maintenance on the OS in supratentorial HGG patients of KPS<80. There are some well-known risk factors such as age at diagnosis, KPS, histological type, distant metastasis, and extent of surgical resection for predicting the OS of patients with HG G [31].

Intravenous and inhalation anesthesias are the common anesthesia methods for HGG resection. But they are different in some aspects. Firstly, intravenous anesthesia inhibits the invasion of the tumor cells and host stress response and protects cellular immunity, while inhalation anesthesia has the opposite effect. Secondly, during craniotomy, the mass effect of the tumor and the peritumoral edema always lead to severe intracranial hypertension and brain herniation. As nearly all inhalational agents increase the cerebral blood flow and ICP, propofol has the opposite effect to decrease the ICP and facilitate tumor exposure. Thirdly, intravenous anesthesia promotes postoperative rapid recovery of the patients. Postoperative pain, nausea and vomiting, and shivering appear less frequently with propofol-maintained anesthesia [16, 33, 34]. However, the hemodynamic stability, time to extubation, and early cognitive functions were similar with two anesthetic techniques [35].

In this RCT study, we will fully evaluate the patients before operation, including physical status, neurological function, and imaging results. During the operation, standard anesthesia management, anesthesia depth monitoring, and individualized medication according to the protocol will be conducted by specially trained personnel. After surgery, the patients will be followed up regularly by designated personnel for the recovery, adverse events, complications, treatment, PFS, and OS.

Although the intervention of our study is intravenous or inhalation anesthesia, inhalational anesthetics will not be used for induction, as it is not routine in clinical practice. So propofol induction will be used in both groups. We regard the effect of a single bolus of propofol as minimal and short, which will be eliminated completely before surgical incision.

We use the survival time to calculate the sample size. As the median OS was 15 vs.11 months in TIVA and inhalation group, with a hazard ratio of 1.66, the calculated sample size is 344, which is more credible in survival analysis.

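### The stated 80% power fits neither reading of the effect size: median OS of 15 vs 11 months implies a hazard ratio of 1.36 under constant hazards, not 1.66, and the time unit of the 0.1 dropout is not given

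*Protocol article*

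**What the plan says.** The protocol article, under Sample size calculation and statistical analysis, specifies "A two-sided Log-rank test with an overall sample size of 344 subjects", split evenly between the arms, and says that this "achieves 80% power at a 0.05 significance level to detect a hazard ratio of 1.66 when the overall survival is 15 vs. 11 months", the longer survival being in the intravenous group. On timing it adds: "The study will last for about 42 months, of which subject accrual (entry) occurs in the first 24 months". Dropout is set at 0.1 for each arm. No time unit is attached to the 0.1, and neither a survival distribution nor a planned number of deaths is given.

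The Discussion repeats the calculation and makes clear that the two survival times are medians: "As the median OS was 15 vs.11 months in TIVA and inhalation group, with a hazard ratio of 1.66".

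Under Outcomes, the primary outcome is OS within 18 months of surgery. Under Data collection and management, the follow-up calls end at month 18.

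**The concern.** The hazard ratio and the two medians are presented as one scenario. A log-rank calculation built from medians, accrual, study length and dropout ordinarily assumes constant hazards, and then the hazard ratio equals the ratio of the medians. Rounding cannot bridge 1.36 and 1.66: on the log scale they differ by a factor of 1.63, so the deaths required differ by a factor of about 2.7.

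At stake is what the trial can be said to detect on its primary outcome. A reader will take it to have an 80% chance of detecting a 4-month gain in median OS. If the 15 vs 11 month scenario under constant hazards is the intended one, the chance is clearly lower, and a null result could be read as stronger evidence of no effect than it is. If 1.66 is the intended effect, the 80% is also wrong under ordinary loss, this time because it is too low.

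**Working it through.** **Inputs.** From the sample size section: two-sided alpha 0.05, power 80%, 172 per group, HR 1.66, 15 vs 11 months, 24 months of accrual in a 42-month study, dropout 0.1 per group. From the Discussion: 15 and 11 are medians. From Outcomes: OS within 18 months. Assumptions not in the article: constant hazards, uniform accrual, exponential loss. Because the unit of the 0.1 is not stated, loss is varied.

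**1. Effect size.** With constant hazards, λ = ln 2 / median, so HR = 15/11 = 1.364. In the other direction, HR 1.66 gives 15/1.66 = 9.0 months against 15, or 11 × 1.66 = 18.3 months against 11.

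**2. Deaths needed (Schoenfeld).** D = 4(1.960 + 0.8416)² / (ln HR)² = 31.40 / (ln HR)².
- HR 1.66: ln HR = 0.5068, D = 122.
- HR 15/11: ln HR = 0.3102, D = 326.

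**3. Reproducing 344.** Of the two-sided variants tried, only one returns the stated size: HR 1.66, medians of 15 vs 9.0 months, follow-up to month 42, and 0.1 lost per month. The death probabilities are then 0.300 and 0.418 (mean 0.359), so N = 122.2/0.359 ≈ 341. A Lakatos Markov log-rank calculation gives N = 345, with power 0.80 at 344. The 11-month median plays no part in this route. No two-sided variant starting from 15 vs 11 months returns 344, nor does HR 1.66 with 10% lost in total.

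**4. Power of 344 patients for 15 vs 11 months.** With loss hazard η and s = λ + η, the probability of an observed death is
- cut at 18 months: (λ/s)(1 − e^(−18s));
- followed to month 42: (λ/s)[1 − (e^(−18s) − e^(−42s))/(24s)].

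Power = Φ(√D × ln(15/11)/2 − 1.960).

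For 10% lost by month 18, η = −ln(0.9)/18 = 0.00585.
- Cut at 18 months: probabilities 0.540 and 0.650, D = 172 × (0.540 + 0.650) ≈ 205. Power = Φ(14.31 × 0.1551 − 1.960) = Φ(0.26) = 0.60.
- To month 42: probabilities 0.689 and 0.785, D ≈ 254. Power = Φ(15.92 × 0.1551 − 1.960) = Φ(0.51) = 0.695.

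A log-rank simulation (4000 runs) gave 0.596 and 0.694.

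| Loss assumption | OS cut at 18 months: deaths, power | To month 42: deaths, power |
|---|---|---|
| None | 214, 0.62 | 270, 0.72 |
| 10% by month 18 | 205, 0.60 | 254, 0.695 |
| 10% per year | 200, 0.59 | 246, 0.68 |
| 10% per month | 110, 0.37 | 115, 0.38 |

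Even with no loss, the expected deaths stay below 326.

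**5. Power of 344 patients if HR 1.66 is kept (10% lost by month 18).**
- Medians 15 vs 9.0: 0.96 cut at 18 months, 0.98 to month 42.
- Medians 18.3 vs 11: 0.94 and 0.98.

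**6. Can both figures hold together?** For Weibull survival with a common shape k, HR = (15/11)^k, so k = ln 1.66 / ln(15/11) = 0.5068/0.3102 = 1.63, a hazard that rises over time. With 10% lost by month 18, power is then about 0.97 (18 months) to 0.99 (month 42).

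**The case against.** The strongest reply is that a hazard ratio need not equal a ratio of medians. The planned log-rank and Cox analyses do not require constant hazards. The Discussion's past tense suggests that the figures may be observed ones, and an observed or adjusted Cox estimate can differ from the ratio of medians. The retrospective source is not available here, so the origin of 1.66 cannot be settled. This stands. A reader might infer that the two figures are mathematically irreconcilable, and the article does not support that: they coexist at a Weibull shape of about 1.63. But no such shape is stated, and under ordinary loss it would give about 97–99% power. The reply therefore saves the pair of figures but not the 80%.

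A reader might also infer that the trial is simply underpowered. That holds for 15 vs 11 months under constant hazards. It does not hold for HR 1.66 with ordinary loss, and the article does not say which effect governs.

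The step 3 reconstruction tempts a further inference, that dropout was entered per month in the software. The inputs are not shown, so this remains a possibility only. It does matter for the range: on that reading, power for 15 vs 11 months falls to 37–38%.

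A one-sided 0.05 test for 15 vs 11 months with 10% total dropout needs about 337–349 patients, close to 344. The article says two-sided, so this does not rescue the statement.

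**Conclusion.** The point holds. The power statement is wrong as written, in both sections where it appears. For median OS of 15 vs 11 months under constant hazards, 344 patients give about 60% two-sided power on the 18-month primary outcome (0.59–0.62 from no loss to 10% per year). Follow-up to month 42 gives about 70% (0.68–0.72), although that goes beyond the stated outcome horizon. If the 0.1 dropout is monthly, power is about 37–38%.

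These figures rest on constant hazards, uniform accrual and exponential loss. Relaxing the first so that both stated effects hold moves power to about 97–99% under ordinary loss, again not 80%. What cannot be determined from the article is which effect the sponsor intended, or the time unit of the dropout.

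**What to change.** In the sample size section and the Discussion, state one effect size, the time unit of the 0.1 dropout, the follow-up horizon (18 months, matching the primary outcome) and the expected number of deaths. Restate the power of 344 patients accordingly, in one of two ways:

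- Keep medians of 15 vs 11 months, write HR 1.36, and give power of about 60% for 18-month OS (about 205 deaths with 10% lost by month 18).
- Keep HR 1.66, replace the medians by a pair that implies it (about 15 vs 9.0 or 18.3 vs 11 months), and restate the power as well: about 94–96% at 18 months with 10% total loss. Changing the medians alone would leave the 80% wrong.

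If the dropout is meant as 0.1 per month, these power figures must be recomputed on that basis. If a non-constant hazard is intended, its shape should be stated and the power recalculated from it.

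The cost is one recalculation and wording in two places. The stated power becomes less favourable if the 15 vs 11 month effect is kept. Restating the power does not itself require more patients; whether to enlarge the trial is a separate decision for the sponsor.

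### 344 patients for 80% power at HR 1.66 does not follow from the stated inputs, and the medians of 15 and 11 months imply a different hazard ratio

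*Protocol article*

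**What the plan says.** In the protocol article, under Sample size calculation and statistical analysis, the test and total are given as "A two-sided Log-rank test with an overall sample size of 344 subjects", with equal groups of 172. The article claims that this size "achieves 80% power at a 0.05 significance level to detect a hazard ratio of 1.66". The survival assumption attached to that claim is 15 months for the intravenous arm against 11 for the inhalation arm. The time frame is given as "The study will last for about 42 months, of which subject accrual (entry) occurs in the first 24 months", and the loss as "the proportion dropping out of the two groups being 0.1, respectively". No time unit is attached to the 0.1.

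The Discussion repeats the basis and identifies the two survival figures as medians: "As the median OS was 15 vs.11 months in TIVA and inhalation group, with a hazard ratio of 1.66".

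Two other sections bear on the calculation. Outcomes defines the primary endpoint as overall survival (OS) up to 18 months after surgery. Data collection and management ends the telephone contacts at month 18.

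**The concern.** Two things do not fit. First, HR 1.66 is a large effect that needs few deaths. With median survival of 11 to 15 months and at least 18 months of follow-up, most patients die under observation, so 344 looks about twice what HR 1.66 requires when only one patient in ten is lost. Second, under exponential survival the ratio of medians is the hazard ratio, and 15/11 is 1.36, not 1.66.

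The two discrepancies pull in opposite directions. Too large an HR lowers N, and whatever else went into the calculation raised it. The 80% is therefore not the power of this design under either stated effect. A reader who takes the effect to be the 15- and 11-month medians would believe the trial has 80% power when it has clearly less.

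**Working it through.** **Inputs from the protocol article.** Two-sided log-rank test, alpha 0.05, power 80%, 1:1 allocation, HR 1.66, medians 15 and 11 months, accrual 24 months, total 42 months, loss 0.1 per group (Sample size section and Discussion); 18-month outcome window (Outcomes). **Assumed here, not stated there:** exponential survival, uniform accrual, exponential loss.

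**Formulas**
- Deaths (Schoenfeld): D = 4(1.960 + 0.842)² / (ln HR)²
- Death hazard λ = ln 2 / median; loss hazard δ
- Probability of an observed death by time t: p(t) = λ/(λ+δ) × [1 − exp(−(λ+δ)t)]. Average it over t uniform on 18 to 42 months for follow-up to month 42, or set t = 18 for the 18-month cut. p̄ is the mean of the two groups.
- N = D / p̄
- Power of 344 = Φ(√(344 p̄ / 4) × ln HR − 1.960)

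**Deaths needed**
- HR 1.66: 4 × 7.849 / 0.5068² = 122.2
- HR 15/11 = 1.364: 4 × 7.849 / 0.3102² = 326.4

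**Trying to reproduce 344 with 0.1 as a proportion of each group.** Each cell runs over three readings of the loss: 10% by month 42, 10% by month 18, and, as a pessimistic end, 10% per year. N is rounded to the nearest whole number.

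| Effect | Window | p̄ | N for 80% | Power of 344 |
|---|---|---|---|---|
| HR 1.66 on the 15-month median | month 42 | 0.790, 0.763, 0.741 | 155, 160, 165 | 0.987, 0.984, 0.982 |
| same | 18-month cut | 0.645, 0.629, 0.616 | 190, 194, 198 | 0.965, 0.962, 0.958 |
| HR 1.66 on the 11-month median | month 42 | 0.731, 0.704, 0.682 | 167, 174, 179 | 0.980, 0.976, 0.973 |
| same | 18-month cut | 0.576, 0.561, 0.549 | 212, 218, 223 | 0.946, 0.941, 0.936 |
| Medians 15 and 11 (HR 1.364) | month 42 | 0.764, 0.737, 0.715 | 427, 443, 457 | 0.710, 0.695, 0.681 |
| same | 18-month cut | 0.610, 0.595, 0.582 | 535, 549, 560 | 0.613, 0.602, 0.593 |

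No row gives 344. Dividing the no-loss N for HR 1.66 (151 or 163) by 0.9 gives about 168 or 181. The Freedman formula raises the deaths for HR 1.66 only to 128. Log-rank simulation (4,000 runs) with 10% lost by month 42, or by month 18 for the cut, gave power of 0.98–0.99 at HR 1.66 (0.94–0.96 with the cut) and 0.71 at the stated medians (0.61 with the cut).

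**What comes close to 344.** Take 0.1 as lost every month (δ = −ln 0.9 = 0.105) and apply HR 1.66 to the 15-month median:
- p = 0.300 and 0.418, so p̄ = 0.3586
- N = 122.2 / 0.3586 = 341 (341–345 by a Lakatos-type calculation, depending on the grid)
- Power of 344 = 0.804 (simulated 0.796)

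This sets the inhalation median at 15/1.66 = 9.0 months instead of 11. The share escaping dropout to month 18, ignoring deaths, would be 0.9^18 = 0.15. The same monthly loss gives 389 with HR 1.66 anchored on 11 months, and 365 with event rates from both stated medians.

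**What 344 patients can detect.** Taking event rates from the two medians and 10% lost by month 18, expected deaths are 344 × 0.737 = 254 (month 42) or 344 × 0.595 = 205 (18-month cut). Then HR = exp(2 × 2.802 / √D):
- D = 254: HR about 1.42
- D = 205: HR about 1.48

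Anchoring on one median, or varying the reading of the loss, moves these only within 1.41–1.43 and 1.47–1.49.

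**The case against.** The strongest defence is that the software run is not in the document. The 0.1 may have been entered as a rate per period, and a cautious loss assumption is the planner's choice. In addition, if the effect really is HR 1.66, the error leaves the trial with more power than claimed, which endangers no conclusion.

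Part of this stands. A reader might infer that 344 arises only from a 10% monthly loss, and so that a dropout-entry error is established. The document does not support that. The match also needs the stated 11-month median to be replaced by 9.0; with the stated medians, the monthly loss gives 365 or 389. Other combinations also land near 344 by discarding a stated input: a one-sided 0.05 test with HR 15/11 and 10% loss gives about 338–349, and reading 15 and 11 as means with a fixed 42-month follow-up and no loss gives 341–346. How the 0.1 was entered is therefore a plausible inference, no more. Nor does the quarterly telephone schedule refute a pessimistic planning rate.

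The defence does not rescue the stated result. As worded, the 0.1 is a proportion of each group, and no such reading yields 344. Surplus power at HR 1.66 is no comfort either, because the protocol also gives the effect as medians of 15 and 11 months, and there 344 falls short.

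**Conclusion.** The point holds in this form: 80% power at HR 1.66 with 344 patients is not a consequence of the inputs given. With 0.1 as a proportion lost, HR 1.66 needs about 155–179 patients (190–223 with OS cut at 18 months). The power of 344 is about 97–99% (94–96% with the cut) at HR 1.66, but about 70% (60% with the cut) at the stated medians.

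It would be wrong to conclude that the trial is simply overpowered and could be made smaller. That is true only if HR 1.66 is the intended effect, and the same sentence contradicts it. The protocol does not settle which of the two is the target.

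The figures rest on exponential survival, uniform accrual and exponential loss. The failure to reproduce 344 is not sensitive to the choice among the overall-loss readings, to Schoenfeld versus Freedman, or to the follow-up window. The cause of the discrepancy remains unknown.

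**What to change.** 1. State the time unit of the 0.1 dropout.
2. Reconcile the hazard ratio with the 15- and 11-month medians, in both the Sample size section and the Discussion, and say which is the target effect.
3. Re-run the calculation with the follow-up window of the primary outcome (18 months per patient, or all follow-up to month 42), and state the survival and accrual assumptions.
4. Replace the claim of 80% power at HR 1.66 with the true figures for 344 patients: 80% power for HR about 1.42 with follow-up to month 42, or about 1.48 with the 18-month cut, and about 60–70% power for medians of 15 and 11 months.

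The cost is one re-run and corrected text in two sections. If the sponsor confirms the medians as the target, the shortfall in power becomes an explicit decision: accept it, or revisit N against the 427–457 (535–560 with the cut) shown above. The Trial status section says that no participant had been recruited, so that decision was still open when the article was written.

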### Randomization and blinding

Block randomization will be conducted via computer-generated codes by an independent research assistant who will pack the allocation sequence with identical sequentially numbered opaque envelopes and distribute to the researcher according to the enrolling sequence. The independent research assistant should not recruit and allocate the participants for the purpose of avoiding selection bias.

Patients will be randomly assigned to the two groups at a 1:1 ratio. At the surgery morning, just before anesthesia induction, the trained attending anesthesiologists will receive the sealed envelope and know about the grouping. They will perform anesthesia strictly following the protocol and record intraoperative information. Trained follow-up personnel will not participate in the clinical anesthesia and postoperative management, or know the records of other researchers. The researcher assistant, patients, and outcome assessors will be blinded to the allocation, intraoperative management, or perioperative information until the completion of the study analysis unless specific circumstances, such as the occurrence of a serious adverse event (SAE).

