#### Secondary outcomes include:

PFS is the duration from the surgery day to the day of first evidence of progression or death within postoperative 18 months. PFS will be evaluated by using the latest-two MRI tests and clinical evidence according to the RANO (response assessment in neuro-oncology) criteria (Supplementary Table 1) [30].Numerical rating scale (NRS) of pain intensity and sleep quality on postoperative 1 to 3 days will be evaluated. Pain intensity score in NRS is 0 to 10, 0 representing no pain and 10 representing the worst pain imaginable. Sleep quality with the NRS (0 = worst sleep, 10 = best sleep) will be used to evaluate the sleep quality at 8 to 10 a.m. every day postoperatively before discharge.Encephaloedema volume will be calculated from MRI assessed by a radiologist at 3 to 7 days postoperatively.Adverse events or complications will be recorded, including congestive heart failure, arrhythmia, myocardial ischemia or infarction, pulmonary edema, pulmonary embolism, respiratory failure, stroke, encephaloedema, hydrocephalus, pneumocranium, intracranial hematomas or infection, epilepsy, gastrointestinal hemorrhage, liver, and kidney dysfunction (Supplementary Tables 2, 3).The length of hospital stay will be calculated and analyzed.

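### A normality pre-test picks the test and summary for the continuous secondary outcomes; for 0–10 pain and sleep scores this mainly distorts the reported size of a half-point difference

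*Protocol article*

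**What the plan says.** In the section Sample size calculation and statistical analysis, the protocol article states: "The Kolmogorov-Smirnov test will be used to test data normality". Variables judged normal are given as mean and SD and compared by t test. For the rest, "Non-normally distributed variables will be summarized as medians and interquartile range (IQR") and the comparison is by Mann-Whitney U test. No outcome is exempted by name. The article does not say whether the test is Lilliefors-corrected, or whether it is run per arm or on both arms together.

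Under Secondary outcomes, pain and sleep quality on postoperative days 1 to 3 are numerical rating scales. For pain, "Pain intensity score in NRS is 0 to 10, 0 representing no pain and 10 representing the worst pain imaginable"; sleep is scored over the same range, with 10 as best. Oedema volume from MRI and length of hospital stay are the other continuous secondary outcomes. The planned size is "172 in the intravenous group and 172 in the inhalation group". Overall survival (primary) and progression-free survival have their own methods (Kaplan-Meier, log-rank, Cox), so the normality rule does not touch them.

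**The concern.** The rule lets the trial's own data choose both the comparison and the summary, by a criterion that says little about which analysis is valid. With 172 per arm, the t test on a bounded 0–10 score does not rely on normality of the scores. The Kolmogorov-Smirnov test, on the other hand, reacts to the ties that whole-number scoring produces, even when the underlying quantity is normal.

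Two things are at stake. First, the scores are usually sent to medians, and the median of a whole-number score moves almost only in whole steps. A modest true difference is then displayed as nothing or as a full point. Second, where the pre-test is not a foregone conclusion, the analysis depends on an unstated choice of variant.

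**Working it through.** **Inputs.** From the article: 344 patients, 172 per arm; 0–10 scales; the two-branch rule; significance at P<0.05. Assumed, because the article gives none: integer scoring, and score SDs of 1.5–3 (1.5–2 for the effect calculations). Scores are modelled as normal values rounded to whole numbers and clipped to 0–10. The plan states no figure for these outcomes or for the normality test, so there is none to reproduce.

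**Step 1: why the pre-test rejects.** For a rounded score centred on a whole number, the empirical distribution jumps by the probability of the modal score. The distance D from the fitted normal curve is then about half that jump before sampling noise, i.e. Φ(0.5/SD) − 0.5:

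- SD 1.5: 0.131
- SD 2: 0.099
- SD 2.5: 0.079
- SD 3: 0.066

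The 5% critical values are:

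- Lilliefors-corrected, 0.895/(√n − 0.01 + 0.85/√n): 0.068 at n = 172 and 0.048 at n = 344.
- Uncorrected, 1.358/√n: 0.104 at n = 172 and 0.073 at n = 344.

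Sampling noise adds to D, so values near or above the critical value mean frequent or certain rejection. Simulated rejection rates (1,000 runs per case, mean 5):

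| Variant | SD 1.5 | SD 2 | SD 2.5 | SD 3 |
|---|---|---|---|---|
| Corrected, n = 172 or 344 | 100% | 100% | 100% | 100% |
| Uncorrected, pooled n = 344 | 100% | 100% | 100% | 99.7% |
| Uncorrected, per arm n = 172 | 100% | 92% | 54% | 31% |

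Repeat runs of the last row gave 54–60% at SD 2.5 and 31–37% at SD 3. Scores with mean 3 and SD 2 gave 98% uncorrected per arm.

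**Step 2: what the median does with a 0.5-point shift (SD 2, 172 per arm).** Take arm means 2.75 and 3.25. In the lower arm, P(score ≤ 2) = Φ((2.5 − 2.75)/2) = 0.450. The standard error of a proportion near one half is √(0.25/172) = 0.038. The chance that the sample median is 3 and not 2 is about Φ((0.5 − 0.450)/0.038) ≈ 0.90. By symmetry the upper arm's median is 3, not 4, with the same chance.

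- Both medians equal 3: about 0.90² ≈ 0.81.
- With means 3.25 and 3.75 the boundary at 3.5 lies between the arms. The medians are 3 and 4 in about 0.81 of trials, and equal in about 2 × 0.90 × 0.10 = 0.18.
- With means 3.0 and 3.5 the upper median is close to a coin toss between 3 and 4.

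Simulation, with ranges over independent runs:

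| Lower-arm mean | Medians equal | Medians differ by 1 |
|---|---|---|
| 2.75 | 79–80% | 15% |
| 3.0 | 47–48% | 47% |
| 3.25 | 13–17% | 79–82% |

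The remainder are mostly half-point differences. At lower-arm mean 2.75, 38–42% of trials combine a significant Mann-Whitney result with identical medians.

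**Step 3: a 1-point shift (same SD and means).** The medians differ by exactly 1 in 80–98% of trials and are equal in only 1–8%.

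**Step 4: power.** For the 0.5-point shift at SD 2, simulated power is about 61–62% for the t test and 59–61% for Mann-Whitney, within about 2 points.

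**Step 5: precision of a mean difference.** Half-width = 1.96 × SD × √(2/172): 0.32 at SD 1.5 and 0.42 at SD 2. Normal-theory power for 0.5 points is 87% and 64%.

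**Step 6: skewed outcomes.** For log-normal data with log SD 0.3–0.5, rejection at n = 344 is 98–100% corrected and 63–100% uncorrected. At n = 172, uncorrected, with log SD 0.3, it is about 20%. For volume and stay, too, the branch taken can depend on the variant and on whether arms are pooled.

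**The case against.** The strongest reply is that the inference barely changes. Mann-Whitney uses all ranks and loses at most about 2 points of power. The IQR is shown beside the median. A significant Mann-Whitney result with equal medians is no contradiction, because the test does not compare medians. Median (IQR) with Mann-Whitney is a defensible choice for bounded scores and skewed volumes. All of this stands, and it limits the point to how the effect is reported.

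Four stronger readings are tempting, and the article does not support them.

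- A reader might infer that the pre-test always rejects for these scores. That holds with the correction or with arms pooled, but not for the uncorrected per-arm test with widely spread scores, and the article does not say which is meant.
- A reader might infer both that the branch is fixed and that it switches from day to day. These cannot hold under the same variant. Under the corrected or pooled test the branch for the scores is in effect fixed. Only the uncorrected per-arm test leaves it open.
- A reader might infer that medians generally hide or double a real difference. That describes differences near half a point; a 1-point difference is usually shown as 1.
- A reader might blame the rule for the lack of an effect estimate with a confidence interval. Neither branch names one, and an article commonly leaves this to the full protocol or analysis plan. Mann-Whitney also has a standard companion, the Hodges-Lehmann shift with its interval, although it too is coarse for whole-number scores.

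The objection does not rescue the rule itself. It is written into the plan, it selects on a criterion that does not matter at this size, and its outcome can depend on an unstated choice.

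**Conclusion.** The point holds as a minor one about reporting of secondary outcomes. The pre-test should not choose the analysis of pain, sleep, oedema volume or length of stay. For whole-number scores it leads almost always to medians under the corrected or pooled variant, and unpredictably (about 31–60% rejection at SD 3 to 2.5) under the uncorrected per-arm variant. With SD 2, a true half-point difference then appears as no difference in about 15–80% of trials and as a full point in about 15–79%, according to where the means fall. Detection is essentially unaffected, and the primary outcome and progression-free survival are not involved. The figures rest on integer scoring and on assumed means and SDs. The direction of the point does not depend on their exact values, but the percentages do.

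**What to change.** Delete the normality pre-test as a decision rule and name one analysis per outcome before unblinding.

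- **Pain and sleep scores:** mean difference between arms with 95% CI (expected half-width about 0.3–0.4 points at SD 1.5–2), with Mann-Whitney as sensitivity analysis and median (IQR) as description.
- **Oedema volume and length of stay:** one effect measure with 95% CI that tolerates skew and zeros, named in advance. Examples are the Hodges-Lehmann shift alongside Mann-Whitney, or a ratio from a log-scale analysis if no zero values can occur.

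The cost is a change of wording and slightly more analysis. No new data, patients or software are needed.
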